## Abstract

**Background:**

As the opioid epidemic continues to have a major negative impact across the US, community pharmacies have come under scrutiny from legal systems attempting to hold them accountable for their role in over dispensing and lack of patient intervention. While the most available tool for monitoring patients’ opioid use is Prescription Drug Monitoring Programs (PDMP), these do not provide pharmacists with actionable information and decision support. Our study addresses this gap through three objectives: [1] incorporate validated opioid risk metric thresholds into a PDMP platform to create the *Opioid Risk Reduction Clinical Decision Support* (ORRCDS) tool; [2] assess ORRCDS’ ability to reduce patient opioid risk; [3] assess ORRCDS’ sustainability and viability for broader dissemination in community pharmacy.

**Methods:**

For objective 1, our team is partnering with leadership from the largest US PDMP organization and a top-five pharmacy chain to implement ORRCDS into the pharmacy chain’s workflow following the Guideline Implementation with Decision Support (GUIDES) framework. For objective 2, our team will conduct a type-1 implementation mixed methods study using a 2-arm parallel group clustered randomized design. We anticipate enrolling ~ 6,600 patients with moderate and high opioid use risk during the 6-month enrollment phase across 80 pharmacies. This sample size will provide 96.3% power to detect a 5% or greater difference in responder rate between the intervention and control arm. Responders are patients with moderate-risk at baseline who reduce to low-risk or those with high-risk at baseline who reduce to moderate or low-risk at 180 days post last intervention. To accomplish objective 3, we will use the Consolidated Framework for Implementation Research (CFIR) to develop and execute cross-sectional qualitative interviews with pharmacists (*n* = 15), pharmacy leaders (*n* = 15), and PDMP leaders (*n* = 15) regarding long term adoption and sustainability of the ORRCDS tool.

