### Objective 2: Testing the ORRCDS

***Design***. To accomplish the second objective of this study of assessing the impact of the ORRCDS tool on patient opioid risk, our study team will conduct a type-1 implementation mixed methods study using a 2-arm parallel group clustered randomized design. This design clusters patients within pharmacy sites, randomized on a 1-to-1 basis to the ORRCDS vs. usual care. We chose the cluster design given its advantages over patient-level randomization and the length of time required by stepped-wedge designs. Regarding patient level randomization, given the real world application of this tool, training staff to deliver the intervention to only some patients within sites and not others would create a greater risk for condition contamination compared to randomizing by site. The cluster design will reduce the possibility of patients being exposed to both conditions, thus preventing contamination. Regarding length of time, a stepped-wedge design that would attempt intervention rollout in 80 busy pharmacy sites would require a prohibitive amount of time for site intervention delivery initiation, intervention utilization, and follow up.

The randomization will be stratified by zip code poverty level and total pharmacy volume of medication dispensed. Stratification by dispensing volume will ensure an even distribution of higher vs. lower volume stores in each condition—given that high volume sites may be more likely to not intervene with each patient given more intense workload. Advantages of site- vs. patient-level randomization include strengthened internal validity from mitigation of potential condition contamination as well as lower costs—given the number of sites and patients involved herein. ORRCDS will be evaluated within two divisions of a pharmacy chain (*n* = 40 intervention pharmacies/*n* = 40 usual care pharmacies) in the state of Ohio. This design includes a 6-month enrollment phase and a 6-month follow up observation phase (see Fig. 2).

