***Sample size and power.*** We anticipate that ~ 6,600 (based on CTN-0093 pharmacy site estimates) moderate/high-risk patients (evaluated by the opioid risk metric) will be enrolled during the 6-month enrollment phase across the 80 pharmacies. The power calculation is presented for multiple scenarios with different assumptions of intraclass correlation (ICC) and effect size (Table 3). The proposed sample size will provide 96.3% power with 2-sided $$\:{\upalpha\:}$$= 0.05 to detect a 3% or greater difference in responder rate between the intervention arm and control arm. Responders are defined as patients with moderate-risk at baseline who reduce to low-risk or those with high-risk at baseline who reduce to moderate or low-risk at 180 days post last intervention. Risk categories are defined by the thresholds identified in CTN-0093, mentioned above [10]. The power consideration assumes an ICC of 0.05, typical for clustered randomized trials of patient’s outcomes [60, 61]. Importantly, the numbers of pharmacies chosen in this study approximates that of a division within the pharmacy chain. Thus, the results herein will have a real-world reference size within the chain pharmacy corporation.

**Table 2 Tab2:** Reach, effectiveness, adoption, implementation, and maintenance implementation science evaluation framework construct chart

Component	Metric	Data source	Assessment timing	Outcome
Effectiveness	Narcotic Score	PDMP	Preintervention, intervention, postintervention	Primary efficacy
	Fatal overdose	Death certificates	Preintervention, intervention, postintervention	Secondary efficacy
	High dose (PQA)	PDMP	Preintervention, intervention, postintervention	Secondary efficacy
	Multiple providers (PQA)	PDMP	Preintervention, intervention, postintervention	Secondary efficacy
	Overlapping benzo (PQA)	PDMP	Preintervention, intervention, postintervention	Secondary efficacy
	Morphine equivalents	PDMP	Preintervention, intervention, postintervention	Secondary efficacy
	Buprenorphine uptake	PDMP	Preintervention, intervention, postintervention	Exploratory efficacy
	# patients approached	CDS tool	Intervention	Primary implementation
Reach	CDS tool use	CDS tool clicks	Intervention	Primary implementation
Implementation	Perceptions CDS barriers	Pharmacists	Pre/post intervention	Secondary implementation
Adoption	Perceptions CDS barriers Disposition on continued CDS use	Pharmacist partner leader interviews	Pre/post intervention	Secondary implementation

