		Pharmacist partner leader interviews	Pre/post intervention	Secondary implementation
Maintenance	Disposition on continued CDS use	PDMP partner leader interviews	Pre/post intervention	Secondary implementation

**Table 3 Tab3:** Power calculation with different assumptions for intra class correlation and effective size

ICC	Design Effect^a^	Total *N*	Effective *N* per arm^b^	Effective Size^c^	Power
0.01	2.24	6600	1471	10%	100
0.01	2.24	6600	1471	8%	100
0.01	2.24	6600	1471	5%	100
0.01	2.24	6600	1471	3%	100
0.01	2.24	6600	1471	1%	97.1
0.03	4.72	6600	698	10%	100
0.03	4.72	6600	698	8%	100
0.03	4.72	6600	698	5%	100
0.03	4.72	6600	698	3%	99.6
0.03	4.72	6600	698	1%	75.5
0.05	7.20	6600	457	10%	100
0.05	7.20	6600	457	8%	100
0.05	7.20	6600	457	5%	100
0.05*	7.20	6600	457	3%	96.3
0.05	7.20	6600	457	1%	57.3
0.1	13.43	6600	246	10%	100
0.1	13.43	6600	246	8%	99.6
0.1	13.43	6600	246	5%	94.7
0.1	13.43	6600	246	3%	78.3
0.1	13.43	6600	246	1%	34.9

^a^Design effect: this is a correction factor that is used to adjust the required sample size due to the clustered randomized design. If a simple randomization is used and the required sample size is N, then to achieve the same power using the clustered randomized design, the sample size should be N times Design effect

^b^Effective *N* per arm: the required sample size to achieve the same statistical power if a simple randomization design is used instead of cluster randomized design. Effective sample size per arm * 2 * design effect = Total N for clustered design

^c^Effective size: the anticipated difference between the 2-intervention arm in responder rate

***Analysis plan***. The primary efficacy endpoint is the responder rate at 180 days post final intervention. We will fit a generalized linear mixed model to relate the primary outcome (i.e., responder status defined based on opioid risk metric) by treatment arm, controlling for baseline covariates including but not limited to the stratification factors, baseline risk level assessment, and other relevant/available patient characteristics, including patient age, sex, insurance status, and location using pharmacy zip code. To model the dichotomous response variable, we will employ the binary distribution with logit link. The random intercept and the unstructured variance covariance matrix will be used to account for within pharmacy correlation. If the model fails to converge, the compound symmetry structured variance covariance matrix will be used.

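### The Abstract attaches 96.3% power to a 5% difference in responder rate, while the Sample size section and Table 3 attach the same 96.3% to a 3% difference

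*Protocol article*

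**What the plan says.** The Abstract, under Methods, gives about 6,600 patients in 80 pharmacies and continues: "This sample size will provide 96.3% power to detect a 5% or greater difference in responder rate between the intervention and control arm". It names no ICC.

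The Sample size and power paragraph under Objective 2 uses the same number of patients and pharmacies. It says "The proposed sample size will provide 96.3% power with 2-sided" alpha of 0.05 "to detect a 3% or greater difference in responder rate between the intervention arm and control arm". It adds: "The power consideration assumes an ICC of 0.05, typical for clustered randomized trials of patient’s outcomes".

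Table 3 marks its base case with a star. That row reads "0.05* 7.20 6600 457 3% 96.3": ICC, design effect, total N, effective N per arm, difference and power. The row for 5% at the same ICC and effective N shows a power of 100. A footnote defines the effect column as the difference in responder rate between the arms.

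**The concern.** The two prose statements share the trial, the planned enrolment, the endpoint and the power to one decimal place. Only the difference to be detected changes, from 5 to 3 percentage points. Both cannot describe the same calculation.

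What is at stake is how the trial is read. The Abstract is the most widely read part of the article, and its readers will take 5 points as the design target. Readers of the Methods will take 3. An observed difference of 4 points would fall short of one and exceed the other. With both figures in print, either could be cited once results are known.

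**Working it through.** **1. Compare the statements.**

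| Place | ICC | Effective N per arm | Difference | Power |
|---|---|---|---|---|
| Abstract | not stated | not stated | 5% | 96.3% |
| Sample size and power | 0.05 | not stated | 3% | 96.3% |
| Table 3, starred row | 0.05 | 457 | 3% | 96.3 |
| Table 3, 5% row, same ICC | 0.05 | 457 | 5% | 100 |

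The four 5% rows of Table 3 read 100, 100, 100 and 94.7 (the last at ICC 0.1). None reads 96.3.

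**2. Reproduce the plan's figure.** Inputs from the article: n = 457 per arm, two-sided alpha 0.05, difference d. The article gives no control rate p0, so it was back-solved; p0 = 0 reproduces the table. The method is a two-proportion z-test with pooled null variance. With p1 = p0 + d and p̄ the mean of p0 and p1:

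power = Φ{[d√n − 1.96√(2p̄(1−p̄))] / √(p0(1−p0) + p1(1−p1))}

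- 3 points: [0.03 × 21.378 − 1.96 × √(2 × 0.015 × 0.985)] / √(0.03 × 0.97) = (0.6413 − 0.3369) / 0.1706 = 1.784. Power is 96.3%, as stated.
- 5 points: [0.05 × 21.378 − 1.96 × √(2 × 0.025 × 0.975)] / √(0.05 × 0.95) = (1.0689 − 0.4327) / 0.2179 = 2.919. Power is 99.8%; the table prints 100.
- 1 point: 57.3%, as stated.

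All 20 cells of Table 3 reproduce within 0.2 points in this way. In the plan's own calculation, 96.3% belongs to 3%.

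**3. Ask what would make the Abstract's pairing true.**

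- Keeping n = 457, 5 points gives 96.3% at a control rate of about 1.8%, which no cell of the table uses.
- Keeping a 0% control rate, n = [(0.4327 + 1.787 × 0.2179) / 0.05]² = (16.44)² ≈ 270 per arm. The design effect would be 3300/270 ≈ 12.2. With the 125 patients per pharmacy from step 4, ICC = (12.2 − 1)/124 ≈ 0.09, which is neither the base case nor a tabulated value.

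**4. Two related checks, outside the mismatch itself.**

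- *Control rate.* Power at n = 457 by assumed control rate:

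| Assumed control rate | 3 points | 5 points |
|---|---|---|
| 0% | 96.3% | 99.8% |
| 1% | 82.9% | 98.5% |
| 5% | 45.2% | 82.0% |
| 10% | 29.5% | 62.8% |
| 20% | 19.6% | 44.0% |
| 50% | 14.6% | 32.7% |

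- *Design effect.* With 1 + (m − 1) × 0.05 = 7.20, m = 125 patients per pharmacy. The article's totals give 6600/80 = 82.5, hence 1 + 81.5 × 0.05 = 5.08 and 3300/5.075 ≈ 650 effective patients per arm. At 650, power for 3 and 5 points is 99.4% and 100% at a 0% control rate, and 39.6% and 77.9% at 10%.

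**The case against.** The strongest reply is that this is a slip in one Abstract sentence. The Sample size paragraph and the starred row agree with each other, so the operative text has a single target. That stands: the design section does not contradict itself, and only the Abstract is out of line.

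Nothing operational hangs on the number, and that stands too. The 6,600 is a forecast from site estimates in the preceding validation study, and the number of pharmacies was chosen to approximate a division of the chain. Neither is solved from a target difference. The primary analysis is a logistic mixed model, and the article sets no decision rule at 3 or 5 points. On the table's figures the Abstract also errs cautiously, claiming 96.3% where the table prints 100.

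The Abstract names no ICC, so it could in principle rest on another scenario. No row of Table 3 supplies one, and step 3 shows that it would need inputs used nowhere in the article.

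A reader might go further and infer that the trial was sized on two conflicting targets, or that the mismatch shows it to be underpowered. The documents support neither. The low powers in step 4 come from replacing the implicit 0% control rate with assumed values. That is a separate question, and its answer varies widely over the range shown.

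**Conclusion.** The Abstract's power statement is wrong against the article's own Methods and Table 3. On the table's inputs (457 per arm, two-sided 0.05, implicit 0% control rate), the mismatch is 96.3% at 3 points against 99.8% at 5. This can be read directly from the text; the recomputation only confirms which pairing the calculation produced. Enrolment, number of sites and analysis are unaffected. It is still more than a typographical matter, because it misstates the headline design claim.

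That the Abstract is the outlier does not prove that 3% was the intended target; only the sponsor can confirm that. Making the sentences agree also does not make 96.3% robust, since it reproduces only with a control responder rate of essentially 0%.

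**What to change.** The sponsor should confirm the design target and state the same difference, with its matching power and ICC, in the Abstract and in the Sample size paragraph.

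- If the target is 3%: change 5% to 3% in the Abstract. Table 3 needs no change.
- If the target is 5%: change the Sample size sentence to 5%, move the star in Table 3 to the 5% row at ICC 0.05, and quote that row's power in both places.

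Either way the cost is one or two sentences and at most the position of the star, with no change to design, enrolment or analysis.

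When restating the figure, the sponsor should also check the implied control responder rate and the patients per pharmacy behind the design effect (125 against 82.5). If either changes, the rest of Table 3 would have to be recalculated. That is a separate and larger task than this correction.

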**Conclusions:**

A PDMP tool that addresses moderate- and high-risk opioid use is not available in community pharmacy. This study will implement ORRCDS in a large retail pharmacy chain that will include additional screening and guidance to pharmacy staff to address risky opioid medication use. Our results will make critical advancements for protecting patient health and addressing the opioid epidemic.

**Supplementary Information:**

The online version contains supplementary material available at 10.1186/s13722-024-00514-1.

## Introduction

The opioid epidemic continues to have a major negative impact across the United States (US; [1]), with overdose rates having significantly increased during the COVID-19 pandemic [2]. Despite shifts in attention on illicitly produced and distributed opioids (e.g., fentanyl), prescribed opioid medications alone or used in combination with synthetic opioids continue to be involved in thousands of overdose deaths annually [1]. Opioid medication misuse is a significant predictor of subsequent overdose [3, 4]. More than 36% of the more than 9 million patients in the US who misused opioid prescriptions (i.e., use of opioid pain medication in a way other than prescribed [5]) in 2021 obtained them through receipt of prescribed medications dispensed through legal means [6]. Overdose deaths from prescription opioids (e.g., oxycodone, hydrocodone) continue to be the second most common source of opioids involved in overdose nationally, with nearly 12,000 deaths in 2022 [7]. Our previous research has consistently demonstrated that 20–40% of patients dispensed opioid medications at community pharmacy settings are engaged in opioid medication misuse [8–10].

Community pharmacies have recently come under close scrutiny from legal systems attempting to hold them accountable for their role in the opioid epidemic for both over dispensing and lack of patient intervention [11–13]. This scrutiny has resulted in large financial penalties and injunctions for practices to improve opioid medication dispensation safeguards and patient intervention services [11–13], such as strengthening prescription drug monitoring, improving medication theft prevention, and limiting oversupplying patients with medications [14]. These actions signal that, in the coming decades, community pharmacies will be required to make significant changes in their policies, workflows, and approaches related to opioid dispensation, stewardship, and patient education.

In addition to the legal impetus pushing pharmacies to greater action related to opioid medication stewardship, a number of benefits exist for these settings that make them a highly attractive location for patient engagement and intervention related to medication misuse reductions. Community pharmacists are among the most accessible health care professionals in the US, with a large majority (more than 90%) of Americans living within *≤* 5 miles of a community pharmacy [15], with many of these locations (more than 40%) having onsite private counseling rooms [16]. Importantly, our previous research has shown that patients are open to pharmacists asking about and discussing their opioid medication use [17].

Given the continued and worsening opioid epidemic, legal exigencies faced, and potential for significant positive impact; it is critical to devise, implement, and test evidence-based strategies and tools to address opioid-related concerns among patients dispensed these medications in pharmacy settings. While the most common tool available to pharmacists for monitoring patients’ opioid use is Prescription Drug Monitoring Programs (PDMP; [18–25]—which have shown positive results for reducing prescribing and limiting days of misuse [19–25]—the efficacy of PDMP alone is unclear regarding its impact on substance use outcomes [22], including rates of overdose [26–28]. A key limitation of PDMPs is the lack of clear and actionable information and decision support available to health care professionals, including pharmacists.

To address these critical gaps in evidence and effective tools, our team proposed, designed, and executed a National Drug Abuse Treatment Clinical Trials Network (CTN) study: *CTN-0093: Validation of a Community Pharmacy-based Prescription Drug Monitoring Program Risk Screening Tool* (i.e., “PharmScreen” [10, 29]). In this project, we collaborated with the largest US PDMP vendor to implement a one-group, cross-sectional health assessment within 19 pharmacies of a top-five largest US chain. The purpose of this assessment and related analyses was to identify clinically meaningful risk thresholds and validate a PDMP-based *opioid risk metric*. The opioid risk metric is an algorithm that weights and sums individual scores for opioid dosages (morphine equivalents), overlapping benzodiazepines and opioid medications, overlapping opioid medications, and numbers of prescribers and pharmacies utilized by patients for opioid dispensing over the last 60, 365, and 730 days—which results in a 2-digit score ranging from 0 to 99. A third digit of the number of active opioid medication prescriptions (1–9, 9 representing 9 or greater prescriptions) is affixed to the end of the score to constitute the full 3-digit score [10, 29]. The gold-standard against which the opioid risk metric was compared was the World Health Organization (WHO) Alcohol, Smoking, and Substance Involvement Screening Test (ASSIST [30, 31]). Study results showed fair concurrent validity for this metric (Area Under the Curve ≥ 0.70; Kappa = 0.35; Spearman correlation = 0.37, *p* < 0.001) and identified low, moderate, and high-risk thresholds anchored to WHO ASSIST risk levels [10].

Having completed this vital groundwork, our team was positioned to move forward with the next steps of (a) implementing the identified risk thresholds into the PDMP platform and then (b) developing a clinical decision support tool for pharmacists. The tool will enable and empower pharmacists to act on the opioid risk metric information. This paper describes the protocol for *CTN-0138: Adaptation and Implementation of a Community Pharmacy-Based Prescription Drug Monitoring Program Opioid Risk Assessment Tool* (i.e., PharmTool; NCT05706311). The PharmTool study has three objectives. The first objective is to implement the opioid risk metric thresholds into the PDMP platform and adapt the platform to create the Opioid Risk Reduction Clinical Decision Support (ORRCDS, pronounced “Orchids”) tool (referred to as ORRCDS or the “tool” throughout this paper). The second objective is to assess the ability of ORRCDS to reduce patient opioid risk. Assessing ORRCDS’ sustainability and viability for broader adoption and dissemination within large-scale pharmacy and corporate environments is the third objective. This paper describes the key design considerations associated with each objective.

## Methods

### Objective 1: Metric implementation and PDMP adaptation

***Design.*** To accomplish the first objective of implementing the opioid risk metric thresholds into the PDMP platform and adapting the platform for intervention delivery, our investigative team is collaborating with leadership from the PDMP partner organization as well as the chain pharmacy organization to incorporate the risk metric thresholds and adapt the PDMP platform for intervention delivery (in the same chain pharmacy corporation mentioned above from CTN-0093). This objective is specifically following the Guideline Implementation with Decision Support (GUIDES) Checklist [32]. The development of GUIDES was originally motivated by the significant potential of decision support tools for implementation of evidence-based practice, yet there have been limited outcomes in previous research literature in terms of use, sustainability, and patient impact [33–35]. Given the complexity of clinical decision support systems, GUIDES was developed by an expert panel to provide structured steps to follow for the development, implementation, and monitoring of decision support tools [32]. GUIDES has four steps, which include: [1] examining the context [2], organizing content [3], ensuring high quality user access, and [4] implementing the ORRCDS tool (see Table 1). Note, steps one and two were targeted for completion within the first ~ four months of the project; step three was targeted for completion within the first ~ 10 months of the project, and step four was targeted for completion within the first ~ 18 months of the project.

The *examining the context* step of GUIDES involved working with the partnering chain pharmacy to assess existing clinical workflow. To do this, we collaborated with compliance and clinical program development pharmacy corporate leaders who understand regulatory and clinical operations related to opioid dispensation to identify optimal opportunities for when the ORRCDS is triggered in workflow. This workflow assessment allowed tool planning to balance optimizing patient management while accommodating practice demands of pharmacists and technicians. Lastly, this step involved working with the PDMP partner as well as the pharmacy compliance and clinical program development leaders to determine actual workflow within the ORRCDS itself for staff use, see Fig. 1.

